### Rescue therapy and concomitant medications

During the entire clinical trial, patients will be prohibited from taking any kinds of drugs or therapies that might affect symptoms related to D-IBS. However, patients are allowed to take a specified medication for abdominal symptoms based on the doctor's judgment as a rescue drug if their D-IBS symptoms are exacerbated beyond a tolerable level. In such cases, the investigator will be informed of the rescue drug administration or it will be documented in their diary.

Patients must report all prescribed and over-the-counter medications taken during the study in their diaries. If patients receive antibiotics for acute infections, symptom data during the time of antibiotic administration and 1 week after completion will be excluded from analysis.

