### Sample size calculation

The present trial has a pilot character of a new therapeutic strategy of GJS and Duolac7S. Similar to the results of a previous study, 12 participants who complete the study can be considered minimal clinical significance [20]. The drop-out ratio is assumed to be 20%. Ultimately, each group will consist of at least 15 participants so the total sample size should be more than 60 participants. This sample size is determined to provide 80% power to demonstrate the superiority of the study agents compared to placebos and a *P*-value < 0.05 will be considered statistically significant.

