#### Pattern analysis of intestinal microbiota

Associations have been observed between IBS patients' symptoms and the presence or quantities of certain gastrointestinal bacteria [31]. In the current study, we will focus on the change in the composition of the intestinal microbiota after administration of the study agents. Each subject will be expected to submit 5 g of fecal samples for bacteriological studies at the baseline (week 0) and at the end of the administration (week 8) periods. The samples will be collected immediately before urine collection and stored at -70°C prior to analysis. The fecal samples will be analyzed in a qualified laboratory (Cell Biotech Co., Ltd., Seoul, Korea) by the denaturing gradient gel electrophoresis (DGGE) method and real-time polymerase chain reaction (RT-PCR), which is a useful genotypic technique for detecting changes in the microbiota [32].

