### Statistical analysis

Statistical analysis of all data will be performed by a specialized statistician in a blind manner. To assess the efficacy of this trial, both the *intention-to-treat *and *per-protocol *populations will be analyzed. Baseline characteristics will be compared by Pearson's chi-square test and analysis of variance (ANOVA). The target variables for analysis in this study include the following: (1) AR and proportion of responders (primary outcomes); (2) VAS for abdominal pain and diarrhea; (3) bowel function scores (frequency, consistency, and ease of passage); (4) severity of individual symptoms (abdominal pain, abdominal discomfort, bloating, flatulence, urgency, and mucus in the stool) and overall symptoms; and (5) IBS-Qol. All values will be presented as mean ± SEM. Comparison between the 4 groups will be performed on the basis of repeated measure ANOVA, and the paired *t*-test will be used to compare between the baseline and after a certain period in each group. The analysis for characteristics such as gender and age between groups will be conducted along with Pearson's chi-square test. All statistical analyses of the data will be performed using the SPSS program, version 16.0 (SPSS Inc., Chicago, IL) and a *P *value < 0.05 will be considered statistically significant.

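### The antibiotic rule deletes observed symptom data from every analysis, which conflicts with the promised intention-to-treat analysis and leaves the responder denominator undefined

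*Protocol article*

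**What the plan says.** All references are to the protocol article.

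- **Rescue therapy and concomitant medications:** for patients given antibiotics for acute infections, "symptom data during the time of antibiotic administration and 1 week after completion will be excluded from analysis". No analysis population is named.
- **Statistical analysis:** for efficacy, "both the *intention-to-treat *and *per-protocol *populations will be analyzed". For the between-group test, "Comparison between the 4 groups will be performed on the basis of repeated measure ANOVA". The software is SPSS 16.0; the procedure within it and the handling of gaps are not described.
- **Interventions:** the other data exclusion, for compliance not above 60% with each product, is expressly confined to the per-protocol analysis.
- **Primary outcomes:** adequate relief is reported at the end of each week. A responder has relief in half or more of the weeks, and the responder proportion is assessed separately for run-in, the 8-week administration period and the 2-week follow-up.
- **Sample size calculation:** 12 completers per arm, 20% drop-out, 15 per arm and 60 in total. It adds: "This sample size is determined to provide 80% power to demonstrate the superiority of the study agents compared to placebos".

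**The concern.** An intention-to-treat analysis compares the groups as randomised and uses the outcomes that were observed, whatever happened afterwards. The antibiotic rule removes observed outcomes because of something that happened afterwards. The removal is neutral only if antibiotic use is unrelated to treatment arm and to symptoms. The article's own rationale makes that doubtful: its background section credits the herbal formula with an effect on infectious diarrhea and on the intestinal barrier, and its discussion expects the probiotic to change the gut flora and strengthen the barrier. If the agents alter the rate of gut infection, the arms lose different numbers of weeks, and those weeks are likely to be symptomatic ones.

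The rule reaches the primary outcomes directly, because both are built from weekly symptom reports. The named method can add to the loss, since a classical repeated measures ANOVA needs a full set of values for each patient.

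**Working it through.** **1. The plan's own figure.** 12 / (1 − 0.20) = 15 per arm, and 4 × 15 = 60. This reproduces. The 80% power cannot be reproduced, because no effect size, standard deviation or response rate is stated.

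**2. Scope of the rule.** Of the two exclusions, the compliance rule carries a per-protocol label and the antibiotic rule does not. Read as written, the antibiotic rule applies to both analyses. It removes a time window, not the patient.

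**3. Weeks affected.** The window is the length of the course plus 7 days. Course lengths are assumed, and the window is taken to lie within the administration period. A weekly report counts as affected if any of its 7 recall days falls in the window.

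| Course (days) | Window (days) | Weekly reports affected, of 8 |
|---|---|---|
| 3 to 7 | 10 to 14 | 2 to 3 |
| 10 to 14 | 17 to 21 | 3 to 4 |

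For a 7-day course, 14 / 7 = 2 reports if the window is aligned with diary weeks, and 3 if it is not. Counting only the reports dated inside the window also gives 2. A 14-day window that starts at week 8 covers the whole 2-week follow-up and leaves 2 − 2 = 0 weeks on which to judge follow-up response.

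**4. Effect on responder status.** Assume independent weeks with relief probability p each (not in the documents) and 2 weeks removed from 8. The chance of being a responder is a binomial tail:

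| p | All 8 weeks, 4 needed | 6 weeks left, 3 needed | Removed weeks count as no relief, 4 of 6 needed |
|---|---|---|---|
| 0.3 | 19% | 26% | 7% |
| 0.4 | 41% | 46% | 18% |
| 0.5 | 64% | 66% | 34% |

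The same patient at p = 0.4 has an 18% or a 46% chance of being a responder, depending on a choice the article leaves open.

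**5. Possible loss in the ANOVA.** This step is conditional. It assumes that weekly values enter, that incomplete patients are dropped, and that nothing is imputed. With antibiotic use a assumed independent of drop-out, patients remaining = 60 × 0.8 × (1 − a). Drop-out alone leaves 48.

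| a (assumed) | Remaining of 60 | Per arm | Power, if 80% at 12 per arm |
|---|---|---|---|
| 5% | 45.6 | 11.4 | 78% |
| 10% | 43.2 | 10.8 | 76% |
| 20% | 38.4 | 9.6 | 71% |

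Power uses the standardised difference that 12 per arm detects with 80% power at two-sided 0.05 (sidedness assumed): (1.960 + 0.842) × √(2/12) = 1.144. Of the total loss, drop-out accounts for 12 patients and the antibiotic rule for 48 − 45.6 = 2.4 to 48 − 38.4 = 9.6.

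**The case against.** The strongest defence is that the rule is pre-specified, worded alike for all arms and applied by a blinded statistician. It also keeps the patient in the data set, so the intention-to-treat population is intact in the sense of who is counted. The aim of judging symptoms free of antibiotic effects is reasonable. All of this stands, but it does not resolve the conflict. A rule worded alike for all arms removes unequal amounts of data if infection rates differ between them, and for the removed weeks the observed outcome is still set aside.

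The second defence is that a journal article need not describe missing-data handling, which may be in a full protocol or analysis plan not shown. That also stands, and it limits the point. Three stronger readings that a reader might infer are not supported:

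- *That the intention-to-treat analysis necessarily becomes a complete-case analysis.* No passage says that incomplete patients are dropped. Imputation, or period means in place of weekly values, would avoid it. A responder can also still be classified with weeks removed.
- *That the intention-to-treat and per-protocol results would nearly coincide.* The compliance threshold separates the two sets, and no rate of non-compliance is given.
- *That week-8 stool samples affected by antibiotics are kept in the microbiota comparison.* The rule speaks of symptom data only, and the list of target variables omits microbiota and permeability. The article is silent on such samples; it does not decide to keep them.

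Figures built on an assumed rate of missed diary entries would not measure the antibiotic rule either, so none is used here.

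**Conclusion.** The point holds as a conflict between stated passages. The antibiotic exclusion, as worded, applies to the intention-to-treat analysis and contradicts its purpose. It changes the primary outcomes, and it leaves the responder definition without a denominator for affected patients. This rests on the text and on the contrast with the compliance rule, and needs no assumed rate.

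The size is not known, because the documents give no antibiotic rate. For one patient with a 7-day course, 2 to 3 of the 8 treatment weeks are affected on the counting stated above. For the trial, the range of about 46 to 38 remaining patients depends on the assumed 5% to 20% use and on the listwise-deletion conditions. It is an illustration, not a forecast. With 15 patients per arm, one reclassified responder moves an arm's proportion by 1/15, or about 7 percentage points, so even rare use could matter. The plan should be corrected, but the flaw does not invalidate the trial.

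**What to change.** Reconcile the sections on concomitant medication, primary outcomes and statistical analysis as follows:

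1. In the intention-to-treat analysis, keep all observed symptom data whatever the antibiotic use.
2. Fix the responder denominator at all weeks of the period concerned (8 for administration, 2 for follow-up). State that a week with no report then counts as a week without relief.
3. Analyse the repeated outcomes with a method that uses incomplete profiles: generalised estimating equations or a logistic mixed model for weekly adequate relief, and a linear mixed model for the visual analog scales.
4. Move the antibiotic-window exclusion to the per-protocol or a sensitivity analysis. State there how a partly covered week is treated and which denominator applies.

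The cost is wording and a change of model, with no new patients or measurements. The downside is that weeks on antibiotics add a little noise to the intention-to-treat estimate; the sensitivity analysis would show how much they matter.

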### Outcome measurements

#### Primary outcomes

Adequate relief (AR) will be used as a primary outcome to evaluate IBS symptom improvement. Patients are expected to report on a weekly basis their response to the following question: "In the past 7 days, have you had adequate relief of your IBS pain and discomfort?" AR will be measured at the end of each week during run-in, administration, and follow-up periods. Responders will be defined as patients reporting AR for at least 50% of the study weeks, which was applied as a major variable in previous studies [20,22]. The proportion of responders, another primary outcome, will be assessed individually during run-in, administration, and follow-up periods.

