**Methods/Design:**

The current trial is a randomized, double-blinded, placebo-controlled, 4-arm study. After a 2-week run-in period, 60 patients with D-IBS will be randomly assigned to one of the 4 combination groups consisting of GJS (water extract granules, 3 g/pack, 3 times a day) with Duolac7S (powder form, 1 capsule, 2 times a day) or their placebos and followed up for 2 weeks. The assigned treatments will last for 8 weeks. The primary outcomes are adequate relief of IBS pain and discomfort and the proportion of responders (on a weekly basis). The secondary outcomes are visual analog scale for IBS symptoms (on a daily basis), quality of life (at 0, 8, and 10 weeks), intestinal permeability, and composition of intestinal microbiota (at 0 and 8 weeks).

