### Design

The current study will be conducted as a placebo-controlled and double-blind trial with 60 patients being randomly allocated to 4 arms. The trial will be implemented at Kyung Hee University Hospital at Gangdong in Seoul, Korea.

Participants will be required to pursue a 2-week run-in (weeks -2 to 0), 8-week administration (weeks 0 to 8), and a 2-week follow-up period (weeks 8 to 10) and to record daily symptoms in a diary.

During the administration period, 1 pack 3 times a day (2 h after each meal) of GJS or its placebo and 1 capsule 2 times a day (2 h after breakfast and dinner) of Duolac7S or its placebo will be provided for 8 weeks. All participants will be divided into 4 groups: (1) the real GJS and real Duolac7S group; (2) the real GJS and placebo Duolac7S group; (3) the placebo GJS and real Duolac7S group; and (4) the placebo GJS and placebo Duolac7S group. The flow of the entire trial is shown in Figure 1.

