### Inclusion criteria

Patients aged 18-75 years with consistent abdominal pain and discomfort should meet the Rome III criteria of IBS [3]. Among IBS subtypes, participants must also be included in the D-IBS type, defined as loose (mushy) or watery stools ≥ 25% and hard or lumpy stools < 25% of bowel movements [3]. The Bristol scale, which is a visual descriptive stool form scale, will be used to assess stool consistency [21]. Patients should not have had structural abnormalities in their intestine detected by colonoscopy in the past 5 years.

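### The responder endpoint takes no account of relief already reported in the run-in, and the stated between-arm analysis names no baseline term to allow for it

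*Protocol article*

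**What the plan says.** The run-in comes before allocation. The abstract states "After a 2-week run-in period, 60 patients with D-IBS will be randomly assigned to one of the 4 combination groups", and the Design section has patients keep a daily diary in the run-in, administration and follow-up periods.

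Under Primary outcomes, "AR will be measured at the end of each week during run-in, administration, and follow-up periods". The responder rule follows: "Responders will be defined as patients reporting AR for at least 50% of the study weeks". It carries no condition on run-in status. The section adds: "The proportion of responders, another primary outcome, will be assessed individually during run-in, administration, and follow-up periods". Read with that sentence, the rule for the 8-week administration period is AR in at least 4 of 8 weeks. Under Secondary outcomes, the VAS scores are also recorded daily from the run-in onward.

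The symptom condition for entry is "Patients aged 18-75 years with consistent abdominal pain and discomfort should meet the Rome III criteria of IBS", plus the D-IBS stool pattern. Neither the inclusion nor the exclusion criteria mention run-in AR or a minimum severity.

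Under Statistical analysis, "Comparison between the 4 groups will be performed on the basis of repeated measure ANOVA", with paired t-tests against baseline inside each group. No baseline covariate is named for the between-arm comparison.

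**The concern.** The first hypothesis is comparative: the combination should do better than either agent alone. The responder count serves that hypothesis only so far as response reflects treatment. Here a patient who answers yes in both run-in weeks and goes on answering yes is a responder in whichever arm they land. Such a patient cannot show benefit on responder status, so each one reduces the difference the trial can see.

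With about 15 patients per arm, a chance excess of a few such patients in one arm also moves the observed difference noticeably. The article holds the information to correct for this. It reports run-in response as a separate result but does not carry it into the comparison between arms.

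The paired t-tests do not help. They are within-arm comparisons and say nothing about differences between arms.

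**Working it through.** **Plan's own figure.** Sample size calculation: 12 completers per arm and 20% drop-out. 12 / (1 − 0.2) = 15 per arm; 15 × 4 = 60. This reproduces. The 80% power cannot be reproduced, because no responder rates are given.

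**Assumptions.** The article gives neither the share f already in relief at entry nor any responder rate. I take f = 10%, 20% and 30%, and suppose these patients respond in any arm.

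**Can an unchanged patient be a responder?** For a constant weekly chance of AR, independent between weeks, the chance of at least 4 of 8 AR weeks is 0.19 at 0.3, 0.64 at 0.5 and 0.94 at 0.7. Patients often in relief at entry would mostly count as responders with no treatment effect at all.

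**Dilution.** If symptomatic patients respond at rates a and b, the arm rates are f + (1 − f)a and f + (1 − f)b. The observed difference is (1 − f)(b − a). For 30% versus 60%:

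| f | Arm rates | Difference | Power, 15 per arm |
|---|---|---|---|
| 0 | 30% vs 60% | 30 points | 0.37 |
| 10% | 37% vs 64% | 27 points | 0.31 |
| 20% | 44% vs 68% | 24 points | 0.26 |
| 30% | 51% vs 72% | 21 points | 0.21 |

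(Normal approximation, two-sided 0.05.) At 12 per arm, 30% versus 83% gives power of 0.78 with f = 0. It falls to 0.69, 0.60 and 0.51 at f = 10%, 20% and 30%.

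**Chance imbalance.** Let X1 and X2 be the numbers already in relief in two given arms, each Bin(15, f). Then P(|X1 − X2| ≥ 3) = 0.121, 0.249 and 0.318 at f = 10%, 20% and 30%.

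Three extra such patients take the place of three symptomatic patients, who would have responded with probability p. The shift is therefore 3(1 − p)/15 = 20 × (1 − p) points: 14, 12, 10 and 8 points for p = 0.3, 0.4, 0.5 and 0.6.

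**Gain from adjusting a VAS outcome.** Take equal variance σ² before and during treatment, and correlation ρ. The relevant variances are σ² for the unadjusted post-treatment value, 2(1 − ρ)σ² for change from baseline, and (1 − ρ²)σ² with the baseline as covariate.

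| ρ (assumed) | Reduction vs unadjusted, ρ² | Reduction vs change, 1 − (1 + ρ)/2 |
|---|---|---|
| 0.5 | 25% | 25% |
| 0.6 | 36% | 20% |
| 0.7 | 49% | 15% |

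**The case against.** **Randomisation spreads these patients over all arms.** This is correct. A reader might infer that active arms are flattered, but the design gives no reason for that. Chance imbalance is also something the significance test already allows for. What remains is lower power and a noisier estimate, in a trial that describes itself as having a pilot character.

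**Entry already requires symptoms.** The criterion asks for consistent pain and discomfort together with Rome III, which is a partial screen. The article gives no share already in relief, and recruitment by mail and newspaper does not establish one. A reader might infer that such patients will certainly be enrolled. The text supports only that they can be, since the criterion has no threshold and is not tied to the run-in or to the AR question.

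**Covariates are commonly left to the analysis plan.** This is fair, and their absence alone would be no finding. Here, however, the article does state a responder rule and a between-arm method, and both can be improved with data in hand.

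**The run-in is used.** Run-in response is reported separately, so an imbalance would be visible, and baseline enters the paired tests. The repeated-measures ANOVA may also include run-in weeks; the text neither says nor excludes this. If it does, the group-by-time term uses them. The group main effect would then average in two weeks in which no treatment effect can exist, so an effect constant over 8 weeks would shrink to 8/(8 + 2) = 80% of its size. Neither reading makes the responder comparison allow for run-in relief.

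**Stool pattern.** A reader might also infer that D-IBS stool form is not confirmed in the run-in. The article names the Bristol scale for that criterion without giving a time window, and the run-in diary may inform it. The text does not settle this.

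**Conclusion.** The point holds as a correctable inefficiency in the primary comparison, not as a bias. The responder rule ignores run-in relief and the stated between-arm analysis names no baseline term, so a patient in relief before treatment can count as a treatment-period responder unchanged.

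On the assumed shares of 10% to 30%, a 30-point difference loses 3 to 9 points. Two given arms differ by 3 or more such patients with probability 12% to 32%. That imbalance should not be read as a full 20 responder points, which would require that symptomatic patients never respond. For p between 0.6 and 0.3 it is 8 to 14 points.

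For VAS, adjustment reduces variance by 25% to 49% against an unadjusted post-treatment comparison. Against change from baseline the reduction is 25% down to 15%, for ρ from 0.5 to 0.7. The larger range should not be quoted alone, because the article does not say which comparison applies.

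All these sizes rest on assumed values of f, p and ρ, since the article gives none. Adjustment will not rescue the power of arms this small, but it improves on the stated method at almost no cost.

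**What to change.** In the Statistical analysis section:

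1. Compare arms on administration-period AR and responder status, adjusted for run-in AR as one covariate (any versus none). More covariates on a binary outcome in about 60 patients would be fragile. If nearly all patients with run-in AR respond, a logistic model may not converge; a stratified (Mantel-Haenszel) difference avoids that.
2. Compare each VAS and stool outcome with its own run-in mean as covariate, and IBS-QoL with its week-0 value. Leave run-in weeks out of the repeated outcome.
3. Pre-specify, as a sensitivity analysis only, the responder comparison in patients with no run-in AR. The subset is defined before randomisation, so the comparison stays randomised, but it is smaller. At f = 20% and 30% versus 60%, it keeps 12 of 15 per arm, with power of about 0.31 against 0.26 for the diluted full set.

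Item 1 corrects for chance imbalance and recovers some precision. It does not undo the dilution of the overall responder difference, which is why item 3 is worth reporting beside it.

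The cost is analysis wording, fixed before unblinding, with no new data. I do not propose a change to eligibility: randomisation has begun (Trial status), and such a change would mix two entry populations.
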